### 1.3 Wearable sensor technology

In recent years, wearables, such as smartwatches and fitness wristbands, have grown in popularity and have gained traction within the healthcare sector for real-time patient monitoring (34). Wearable devices have evolved gradually in the form of accessories, integrated clothing, body attachments and body inserts. The advanced sensors and increased connectedness of these devices will allow individuals to monitor and manage their own health with ever-greater accuracy. The investigation of the potential of available wearable technologies in the detection and monitoring of COVID-19 patients by the scientific community has recently been emphasized (35).

### 1.4 COVID-RED project summary

In this project, we will evaluate the use and performance of the Ava bracelet, a device that uses three sensors to measure the wearers' breathing rate, pulse rate, skin temperature, perfusion and heart rate variability while they sleep. Initially developed to detect menstrual cycle changes among ovulating women for which it is CE-marked (36–38), the bracelet's underlying technology and hardware are gender agnostic; we aim to test whether this wearable device could be repurposed and its algorithms customized to detect pre-symptomatic COVID-19 infection in general and high-risk populations based on deviations in measured physiological parameters. The Ava bracelet integrates with a complementary mobile application (Ava-COVID) which also allows users to log any symptoms they may be experiencing along with potential confounding factors in a Daily Symptom Diary. Within the app, machine learning algorithms based solely on data from the Daily Symptom Diary (control condition) or on data from both the Daily Symptom Diary and the Ava bracelet (experimental condition) will provide real-time feedback to the subjects about potential infection status (36–38). We hypothesize that the algorithm based on the Daily Symptom Diary and bracelet in combination will perform better at detecting SARS-CoV-2 infection in general and, in the case of symptomatic infection, earlier than the algorithm based solely on the Daily Symptom Diary.

In this randomized, single-blind, 2-period crossover study we will follow up to 20,000 subjects in the Netherlands who will each log symptoms and wear the Ava bracelet up to 9 months. The study will start with an initial Learning Phase, followed by a 3-month Period 1 and a 3-month Period 2. Each subject will undergo the control condition in one of these periods and the experimental condition in the other period, but the order will be randomly assigned. 10,000 subjects will be assigned to each period sequence stratified by risk-level, with approximately 6,500 from a general (normal-risk) population and 3,500 from a high-risk

population (see Table 1). Subjects entering the study at the end of the recruitment period may directly start with Period 1 and will not be part of the Learning Phase.

During the study, the algorithms in both the control and experimental conditions will provide real-time prediction to subjects whether they likely have an active SARS-CoV-2 infection. Individuals with a suspected SARS-CoV-2 infection based on these algorithms will be encouraged to get tested using the existing testing infrastructure in the Netherlands provided by the Municipal Health services (GGD). At the moment of writing, the GGD offers free SARS-CoV-2 polymerase chain reaction (PCR) and antigen testing services. While in this protocol tests to confirm current SARS-CoV-2 infection are described as PCR and/or antigen tests, results from other validated testing methods used by the GGD will also be documented and processed in the same way, should the GGD choose to expand the type of tests being used to detect SARS-CoV-2 infection in Dutch residents. Subjects who are thought to have an SARS-CoV-2 infection according to the algorithm of the control or experimental condition, but are rejected for testing by the GGD, will be advised to use self-sampling kits provided by the study team which they can send to the central laboratory for testing. A reason for such rejection by the GGD may include not (yet) having overt symptoms of a respiratory tract infection plus not having any evidence (such as a GGD or CoronaMelder app notification) of having been in close contact with someone who tested SARS-CoV-2-positive. In addition, fingerstick capillary blood samples will be collected from COVID-RED subjects at baseline, after the Learning Phase (if applicable) and after the completion of each period. Samples collected after the Learning Phase and the completion of Period 2 will be tested for SARS-CoV-2 antibodies to determine whether the subject had a previous SARS-CoV-2 infection prior to the study or during the test periods (which was not detected through real-time SARS-CoV-2 infection testing). Baseline samples of subjects will only be analysed if the sample collected at the end of the Learning Phase is positive for SARS-CoV-2 antibodies or if the subject entered the study at the end of the recruitment Period. Samples of subjects collected at the end of Period 1 will only be analysed if the sample collected at the end of Period 2 is positive for SARS-CoV-2 antibodies.

This design and infection testing strategy will enable a proper evaluation of the algorithms in the setting of asymptomatic cases, pre-symptomatic cases, or when individuals lack respiratory symptoms. The sensitivity and specificity of the algorithms used in both study conditions will be assessed and compared. In addition, the bracelet's ability (on top of the daily symptom diary data) to detect early or asymptomatic infections will be assessed within all subjects. This analysis will allow subjects to serve as their own controls, testing the potential efficacy of the app plus bracelet over and above the effects of symptom reporting

alone. In conclusion, this project will deliver a large body of information on SARS-CoV-2 and COVID-19 prevalence and incidence in addition to validating remote vital signs and self-reported symptom monitoring systems for early infection detection.

## 2. OBJECTIVES

### 2.1 Primary Objectives:

Using laboratory-confirmed SARS-CoV-2 infections (detected via serology tests, PCR tests and/or antigen tests) as the gold standard, we will determine the sensitivity, specificity, positive predictive value (PPV) and negative predictive value (NPV) for each of the following two algorithms to detect *first-time* SARS-CoV-2 infection including early or asymptomatic infection: the algorithm using Ava Bracelet data when coupled with the self-reported Daily Symptom Diary data, and the algorithm using self-reported Daily Symptom Diary data alone. In addition, we will determine which of the two algorithms has superior performance characteristics for detecting SARS-CoV-2 infection including early or asymptomatic infection as confirmed by SARS-CoV-2 virus testing.

### 2.2 Secondary Objective(s):

1. To assess the health economic utilization of a wearable device and mobile application as measured by endpoints such as:
  - a. Number of tests for suspected SARS-CoV-2 infections
  - b. Number of hospitalizations
  - c. Number of ICU events
  - d. Number of days requiring breathing support (e.g. oxygen and/or ventilation)
2. To determine the incidence of SARS-CoV-2 infection during the study
3. Identify which features of the Ava bracelet and Daily Symptom Diary are the most predictive features
4. Assess the independent predictiveness of an algorithm derived from physiological data gathered by the Ava bracelet in addition to self-reported daily symptom data
5. To assess the time from algorithm indication to symptom onset in the subject
6. To assess the time from algorithm indication to testing of the subject
7. To determine how taking antipyretic medication affects physiological parameters among subjects using the Ava bracelet and Daily Symptom Diary
8. To determine how self-reported vaccinations cause changes in biophysical parameters from subject's given baseline measurements
9. To correlate the longitudinal symptoms reported by study subjects confirmed to have COVID-19 with changes over time in their physiological data
10. To characterise longitudinal symptoms and recovery dynamics reported by the study subjects to the presence or absence of lab-confirmed SARS-CoV-2 infection
11. To assess the adherence to daily symptom diary completion and Ava bracelet wearing and synchronising over time

12. To determine the time necessary to establish baseline physiological parameters per subject in the Learning Phase of the study
13. To determine if retrospective identification of the moment of potential SARS-CoV-2 infection is possible for subjects who are seropositive at the end of a period but were negative at baseline and did not receive an alert to get tested during the study
14. To determine the rate of breakthrough and asymptomatic COVID-19 infections among vaccinated individuals
15. To assess the influence of self-reported COVID-19 vaccinations on compliance to study procedures

### **2.3 Exploratory Objective(s):**

1. To assess how vaccination by different vaccines and across time affects the trajectory of SARS-CoV-2 infection
2. To determine whether other general, non-COVID-19 respiratory infections (as measured by self-reported symptoms and a negative diagnostic or antibody test for COVID-19) can be detected earlier by changes in physiological parameters
3. To determine whether COVID-19 differs from other respiratory illnesses in biophysical changes from baseline during the pre-symptomatic period
4. To determine whether women using hormonal contraception (HC) are less likely to contract SARS-COV-2 than menstruating women not on HC or menstruating women on non-HC
5. To determine whether normally menstruating women not on HC are more susceptible to infection by SARS-CoV-2 based on where they are in their menstrual cycles

### 3. STUDY DESIGN

#### 3.1 Design

COVID-RED is a randomized, single-blinded, two-period, two-sequence crossover trial. 20,000 subjects will be recruited, randomized 1:1 to either Sequence 1 (experimental condition followed by control condition) or Sequence 2 (control condition followed by experimental condition). The study will start with a Learning Phase (maximum of 3 months), followed by Period 1 (3 months), and Period 2 (3 months) (Table 1). All subjects will be instructed to log symptoms in the Daily Symptom Diary within the Ava COVID-RED app, and wear the Ava bracelet each night and synchronise it with the app each following day, throughout the full period (up to 9 months) of their study participation. In the Learning Phase baseline physiological parameters of subjects will be determined and data will be collected for further algorithm development. Subjects will receive real-time recommendations (for example, to get tested) based on data from the Daily Symptom Diary and/or physiological data from the Ava bracelet. Subjects entering the study at the end of the recruitment period may directly start with Period 1 and will not be part of the Learning Phase.

After completion of the Learning Phase subjects will move into Period 1, followed by Period 2, and will be unaware whether the feedback they receive during these periods is based on the Daily Symptom Diary data alone (control condition) or based on the diary and bracelet data (experimental condition). Based on demographics, medical history and/or profession, each subject will be stratified at baseline into a high-risk and normal-risk group within each sequence. This results in approximately 6,500 normal-risk individuals and 3,500 high-risk individuals per sequence. See Table 1 for a tabular representation of this design.

Table 1 Crossover trial design for COVID-RED

|                                                               | Learning Phase
(up to 3 months) | Period 1
(3 months) | Period 2
(3 months) |
|---------------------------------------------------------------|-------------------------------------------|-------------------------------|-------------------------------|
| Sequence 1
(6,500 normal-risk &
3,500 high-risk) | Algorithm training &
baselining        | Experimental
Condition     | Control
Condition          |
| Sequence 2
(6,500 normal-risk &
3,500 high-risk) |                                           | Control
Condition          | Experimental
Condition     |

### 3.2 Data collection

The primary objective of this study is to evaluate the ability to detect SARS-CoV-2 infections using the Ava bracelet when coupled with the Daily Symptom Diary using the Ava COVID-RED app as compared to a control condition in which data from the Ava bracelet is disregarded in the applied algorithm. This is a reasonable control condition choice to assess an incremental gain. As such, two main methodologies will be used to obtain relevant data from subjects throughout the study to assess the primary objective:

- The Ava bracelet will track daily changes in wrist skin temperature, respiratory rate, and pulse rate. While subjects will wear and synchronise this data throughout the study, data from the bracelet will inform the applied machine learning algorithm only in the experimental condition and in the Learning Phase of the study.
- The Daily Symptom Diary included in the Ava COVID-RED app allows subjects to self-report daily on experienced symptoms and other relevant information (e.g., alcohol consumption). Data from the Daily Symptom Diary will always inform the applied algorithms throughout the study.

### 3.3 Implementation and development of algorithms

For both the control and experimental conditions, separate algorithms will be applied. For the control condition, an algorithm meant to predict potential active SARS-CoV-2 infections will be applied that incorporates deterministic expert-based rules regarding the presence of SARS-CoV-2 symptoms defined by the Dutch national institute for public health and the environment ‘Rijksinstituut voor Volksgezondheid en Milieu’ (RIVM) guidelines (at the time of writing these include: common cold symptoms [such as a nasal congestion, runny nose, sneezing, sore throat], coughing, shortness of breath, elevated temperature or fever, and sudden loss of smell and/or taste [without nasal congestion]). Any subject that experiences any of the above symptoms will be advised to get tested. For the experimental condition, a machine learning algorithm developed for the same purpose based on both symptom and confounder data as well as physiological parameters collected through the Ava bracelet will be applied on data collected during the study from the Daily Symptom Diary and the Ava bracelet. Both algorithms will give recommendations to the subjects whether they should get tested for SARS-CoV-2 infection. For the algorithm in the experimental condition to give a recommendation based on physiological data, it is first required to establish a baseline per subject of their “normal” physiological patterns. The period of time in which this baseline is determined is referred to as “baselining”. This will take place when subjects enter the study and will not be repeated within each period of the crossover portion of the trial. As soon as a stable baseline has been determined for all measured physiological parameters, the algorithm can start detecting when there are significant deviations from this baseline. For the

remainder of the Learning Phase the experimental condition algorithm will be applied for subjects that are part of this Phase. In Period 1 and 2, data from only the Daily Symptom Diary (control condition) or both the Diary and the bracelet (experimental condition) will be used to inform the algorithms that give indications to the subjects whether they should seek testing.

In the Learning Phase and Period 1 of the study, versions of the algorithms will be applied that have been developed and trained using data accrued during an ongoing feasibility study in Liechtenstein (COVI GAPP study) and proprietary historical data from Ava Fertility Tracker bracelet users. These will be collectively referred to as the version 1 (V1) algorithms. Data collected during the Learning Phase of this study will be used to update and inform the algorithms which will then be implemented in Period 2. These versions of the algorithms will be collectively referred to as the version 2 (V2) algorithms. As such, Period 1 and 2 will evaluate different versions of the algorithms and provide insight into the possible improvement of the algorithms over time due to the increased availability of data for development. The applied version of the algorithms at different moments in the study will be taken into account during the statistical analysis. The final version of the algorithm (version 3; V3), which will be developed using all the data collected during the study, will also be applied retrospectively to all subjects, thereby enabling investigation of how the algorithm performed as compared to earlier versions. See Figure 2 for an illustration of this process.

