#### 4.4.2 Early detection analysis

The second statistical analysis that will be performed for the primary objective concerns the timing of each study condition to detect SARS-CoV-2. The time to first SARS-CoV-2 indication or infection will thus be compared between the conditions. This will be tested using a stratified log-rank test. Frequently, power calculations for the log-rank test assume some form of proportional hazards or a specific parametric family for the study arms. In this study, we expect the experimental condition to be able to detect SARS-CoV-2 infection earlier due to the possible detection of pre- or asymptomatic individuals due to deviations in physiological parameters. However, when subjects become symptomatic, the algorithms in both the control and experimental condition will each declare subjects to likely be infected at the same moment by definition. To account for this aspect, a piecewise log-rank test power calculation is used to characterize the trial power. The assumption in the piece-wise hazards is that initially the experimental condition will have a higher chance to detect SARS-CoV-2 infection; however, this difference will decrease over time resulting in equal hazards in the later pieces of the hazard function. As described in the first analysis above, the proposed crossover design results in an application of bootstrap statistical testing so that the power calculations in Table 5 are rough approximations. The estimated power is bounded below by a parallel-arm study with 10,000 subjects per condition and above by a study with 20,000 subjects per condition. From these bounds it appears that the trial is well powered under all of the recently reported RIVM data.

Table 5: Lower (10,000) and upper (20,000 ) bounds of the trial power for a piecewise log-rank test to detect differences between study conditions on the time to first SARS-CoV-2 indication or infection based on infection rates of Weeks 36 through 40 of 2020

|              | Week 36 |      | Week 37 |      | Week 38 |      | Week 39 |      | Week 40 |      |
|--------------|---------|------|---------|------|---------|------|---------|------|---------|------|
|              | 10k     | 20k  | 10k     | 20k  | 10k     | 20k  | 10k     | 20k  | 10k     | 20k  |
| Power | 0.66    | 0.92 | 0.80    | 0.98 | 0.94    | 0.99 | 0.99    | 1.00 | 1.00    | 1.00 |

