#### *Comparison between study conditions and within-subjects*

For the primary comparison between study conditions, the control condition will act as a reference group towards the experimental condition for Period 2. By directly comparing both study conditions within the crossover design, the added benefit can be assessed of including the Ava bracelet data for the detection of potential SARS-CoV-2 infections. In addition to the evaluation within Period 2, control vs. experimental comparisons will be made using both periods via application of bootstrapping methods detailed further below. In addition, a within-subjects analysis will be performed using all subjects as they will all wear and synchronise the bracelet throughout the trial. This allows for an extra within-subject analysis of the ability of the algorithm based on the symptom data with or without the bracelet data to detect early and asymptomatic SARS-CoV-2 infection.

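### The protocol contradicts itself on what the two conditions run; if section 3.3 governs, the randomised Period 2 contrast does not isolate the bracelet

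*Protocol*

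**What the plan says.** Section 3.3 specifies the algorithms and says that they are separate. The control algorithm "incorporates deterministic expert-based rules regarding the presence of SARS-CoV-2 symptoms", based on the national (RIVM) list, and the passage continues: "Any subject that experiences any of the above symptoms will be advised to get tested". The experimental condition runs "a machine learning algorithm developed for the same purpose based on both symptom and confounder data as well as physiological parameters" from the bracelet. Confounders are named only on the experimental side.

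Other sections describe the conditions differently:

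- Section 1.4 speaks of "machine learning algorithms based solely on data from the Daily Symptom Diary (control condition".
- Section 3.2 describes "a control condition in which data from the Ava bracelet is disregarded in the applied algorithm" and comments: "This is a reasonable control condition choice to assess an incremental gain".
- Section 10 (Development and validation of algorithms) says that Learning Phase data serve to train both algorithms.
- Section 3.4 defines the red light for both conditions: either a significant biophysical change or RIVM symptoms. Section 8.4.11 repeats this and adds background medical information to the control's inputs.
- Section 4.4.2 says that once subjects are symptomatic, "the algorithms in both the control and experimental condition will each declare subjects to likely be infected at the same moment by definition".

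Section 10 (Comparison between study conditions and within-subjects) places the primary comparison in Period 2 and says that by comparing the conditions directly "the added benefit can be assessed of including the Ava bracelet data for the detection of potential SARS-CoV-2 infections". Section 10.2 adds a retrospective within-person comparison of the fully developed algorithm with and without bracelet data, using McNemar's test.

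**The concern.** The project's question is what the bracelet adds to symptom reporting. A randomised contrast answers it only if the conditions differ in the bracelet and nothing else. As section 3.3 is written they also differ in how the diary is turned into an alert (fixed rule or learned model) and in whether confounders are used. Randomisation balances subjects; it does not separate components bundled in one condition.

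A Period 2 gain could then come from a model that reads the diary better than the rule, with the bracelet contributing nothing. Equally, a real bracelet contribution could be hidden if the learned reading of the diary loses sensitivity. The other sections describe conditions for which this problem is absent or different, so the document does not settle what its primary comparison tests.

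**Working it through.** **1. The descriptions side by side**

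| Protocol section | Control | Experimental | Does the contrast isolate the bracelet? |
|---|---|---|---|
| 3.3 | Deterministic RIVM rules | Machine learning on symptoms, confounders, bracelet | No |
| 1.4 | Machine learning on diary | Machine learning on diary and bracelet | Yes, if otherwise built alike |
| 3.2 | Applied algorithm, bracelet data disregarded | Same with bracelet data | Yes |
| 10 (development) | Trained on Learning Phase data | Trained on Learning Phase data | Depends on what is trained |
| 3.4, 4.4.2, 8.4.11 | Red on RIVM symptoms | Red on RIVM symptoms or bracelet deviation | Yes |

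These cannot all be true. A fixed guideline rule is not trained. A free-standing model that takes symptoms as inputs does not guarantee an alert at the same moment as the rule, which is what section 4.4.2 assumes for its power calculation.

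**2. What the contrast estimates under section 3.3**

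Let S be sensitivity or specificity.

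S(model, bracelet) − S(rule) = [S(model, bracelet) − S(model, no bracelet)] + [S(model, no bracelet) − S(rule)]

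The first bracket is the bracelet's contribution, the second the change of diary method and use of confounders. The Period 2 contrast gives only the sum, because neither condition runs the model without the bracelet.

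Under the shared-trigger reading the second bracket is zero by construction. The experimental alerts are then the control alerts plus extra ones, so expected specificity cannot exceed the control's.

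**3. A clue in the protocol's own planning**

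Table 4 (its caption says sensitivity, its rows specificity) plans for differences of −3%, −1.5%, +1.5% and +3%. If the sign means experimental minus control, which is not stated, the positive rows do not fit the shared-trigger reading and do fit section 3.3.

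**4. How readily a diary-method shift would be declared significant**

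Inputs: 10,000 per arm (4.4.1); two-sided 0.05 (10); positive share from Table 2. For Week 36, 5,427/180,182 = 3.01%; for Week 40, 23,264/223,274 = 10.42%. Non-infected per arm over the five weeks: 9,699, 9,600, 9,409, 9,201 and 8,958.

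Formula (normal approximation): power = Φ[(d − 1.96·se0)/se1], with se0 = √(2·p̄(1−p̄)/n) and se1 = √([p1(1−p1) + p2(1−p2)]/n).

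The protocol states no baseline specificity, so Table 4 can only be back-fitted. A baseline of 0.825 matches 19 of 20 cells within 2 points:

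| Difference | Table 4, Weeks 36–40 | Computed at 0.825 |
|---|---|---|
| −1.5% | 0.79, 0.78, 0.75, 0.76, 0.73 | 0.77, 0.77, 0.76, 0.75, 0.74 |
| +1.5% | 0.82, 0.79, 0.77, 0.76, 0.76 | 0.80, 0.79, 0.79, 0.78, 0.77 |
| ±3% | 1 throughout | 1.00 throughout |

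Worked cell, Week 36, +1.5%: p1 = 0.825, p2 = 0.840, se0 = se1 = 0.00536; (0.015 − 1.96 × 0.00536)/0.00536 = 0.84; Φ = 0.80.

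Now suppose that section 3.3 governs, the bracelet adds nothing, and the learned reading of the diary alone raises specificity. Probability of a significant result (Week 36, Week 40):

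| Assumed baseline | +1.5 points | +3 points |
|---|---|---|
| 0.30 | 0.62, 0.59 | 0.99, 0.99 |
| 0.50 | 0.55, 0.52 | 0.99, 0.98 |
| 0.70 | 0.63, 0.60 | 1.00, 0.99 |
| 0.825 | 0.80, 0.77 | 1.00, 1.00 |
| 0.90 | 0.95, 0.93 | 1.00, 1.00 |

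This shows that the trial would pick up a small shift from any source. It does not show that such a shift exists.

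**5. Whether the planned within-person comparison repairs this**

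It varies only the bracelet input, which is the right contrast. But section 10.2 applies it to the fully developed algorithm, and section 3.3 builds the final version (V3) from all data collected in the study, Period 2 included. It therefore tests a model on data used to develop it, and the model is not the V2 deployed in Period 2.

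**The case against.** The strongest case against is that the endpoint's own definition shares the diary logic. The primary analysis counts red lights, and sections 3.4 and 8.4.11 define red as a biophysical change or RIVM symptoms, the first of them expressly for both conditions. Section 4.4.2 agrees. Section 3.3 says only that the control algorithm incorporates rules, its advice to test on any listed symptom is not expressly confined to control subjects, and nothing says that the experimental model may stay silent on an RIVM symptom. Within-person comparisons are also planned, and comparing a whole system with national symptom criteria is a legitimate pragmatic question.

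Much of this stands. A reader might infer from section 3.3 that the randomised contrast cannot show the bracelet's added benefit. The documents do not support that as a general statement, because under sections 3.4, 4.4.2 and 8.4.11 it would. A reader might also attach a size, for example a spurious 3 to 25 points from specificities of 0.60 for the rule and 0.63 to 0.85 for a diary-only model. Those values appear nowhere in the protocol, and under the shared-trigger text no such gain could arise.

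The contradiction itself remains: the algorithm section does not read like the red-light section, and Table 4's positive differences leave the section 3.3 reading alive. The pragmatic comparison is legitimate, but it is not the one the protocol says it makes.

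**Conclusion.** The point holds as an unresolved contradiction with a conditional consequence. The protocol gives incompatible accounts of what each condition runs, and the meaning of the primary comparison depends on which is true. If section 3.3 governs, the Period 2 contrast estimates the combined effect of diary method, confounder use and bracelet, and sections 3.2 and 10 claim too much in crediting it to the bracelet. If the shared-trigger text governs, that attribution stands and section 3.3 is misworded.

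No size can be given for the misattribution. What can be said, on the section 3.3 reading with a bracelet that adds nothing, is that a diary-method shift in specificity would be declared significant with probability 0.52 to 0.95 at 1.5 points and at least 0.98 at 3 points, over assumed baselines of 0.30 to 0.90. The retrospective comparison on the final algorithm does not settle the matter for V2.

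**What to change.** Reconcile sections 1.4, 3.2, 3.3, 3.4, 4.4.2, 8.4.11 and 10 (Development and validation of algorithms) so that each says the same about what each condition runs: its inputs, whether it is a rule or a trained model, and what turns the light red.

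If the diary logic proves identical in both conditions, correcting the text is enough. If not:

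- Describe the randomised contrast in sections 3.2 and 10 as the whole system (machine learning with diary and bracelet) versus the symptom rule.
- Before Period 2, lock a diary-only companion to V2, built by the same pipeline on the same Learning Phase data with the bracelet inputs removed.
- Score V2 and the companion silently on all Period 2 subjects, and base any claim about the bracelet's added benefit on the paired comparison of the two.

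The cost is one extra model fit, background scoring on data already collected (all subjects wear and synchronise the bracelet throughout), and edits to the text. No alert shown to a subject changes. The downside is a narrower claim from the randomised contrast.
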